In the context of SCED studies, randomization does not refer to individuals being randomly allocated to treatment groups, but to the random onset of the intervention phase which is usually set within a fixed window of time in order to make this randomization more feasible [38]. In this study, a window of 9 to 24 measurement points (i.e. 3 to 8 weeks at the set frequency of three test assessments per week) will be employed in which the change of phase from baseline to intervention phase will be randomly determined. This determination will be done with a random number generator in Excel set to give a random number between 9 and 24. There will be a baseline phase ranging from 3 to 8 weeks, followed by an intervention phase of 12 weeks and a final follow-up phase of 3 weeks after a 12 week rest period with no measurements and no interventions. As we will exclude the first 4 measurements in the baseline phase from analysis, see Sect. "Statistical analysis", this leaves us at least 5 measurement points in this phase, 36 measurement points in the intervention phase and 9 measurement points in the follow-up phase. Neither participants nor researchers will be blinded to the phase of the intervention. Replication of the experiment will be done in 15 participants.

Finally, additional measurements will be done in a repeated manner according to a single-armed prospective design before baseline phase, at the end of the baseline phase, at the end of the intervention phase and at the start of the follow-up phase.

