##### Randomization test

Subsequently, randomization tests will be performed to test the null hypothesis that NMES does not have an effect on participant’s cognitive function. The observations of the baseline phase will be compared to those of the intervention and follow-up phases respectively. The test statistic “means of phase A minus means of phase B” will be chosen as the primary outcome of this study. In case visual analysis suggests delayed effects, the randomization test will be repeated with lagged data until the lowest p-value has been reached (one effect lag equals one day). The first 4 measurements in the baseline phase will be removed before calculating the means, since we expect a learning effect on the first trials, leaving between 5 and 20 measurement points depending on the randomly decided length of the baseline period. Studies that tested the statistical properties of a randomization test used in this type of design showed that the Type I error probability of the randomization test was maintained at an acceptable level [61].

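### The planned randomisation test of baseline against follow-up cannot show whether an effect is retained, because only the start of the intervention is randomised

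*Protocol article*

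**What the plan says.** All of this is in the protocol article.

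- **Comparisons.** The Randomization test section states: "The observations of the baseline phase will be compared to those of the intervention and follow-up phases respectively". So a randomisation test is planned for A versus B and for A versus C.
- **Statistic.** The same section names the signed difference "means of phase A minus means of phase B" as the primary outcome. It gives no separate statistic for A versus C and does not state sidedness.
- **What is random.** In the Study design section, "the change of phase from baseline to intervention phase will be randomly determined", within "a window of 9 to 24 measurement points". The section explains randomisation in this type of design as "the random onset of the intervention phase which is usually set within a fixed window of time".
- **Follow-up.** Phase C is "a final follow-up phase of 3 weeks after a 12 week rest period with no measurements and no interventions". The phase sizes are "36 measurement points in the intervention phase and 9 measurement points in the follow-up phase".
- **Trimming.** "The first 4 measurements in the baseline phase will be removed before calculating the means", so phase A contributes 5 to 20 values.
- **Which points can switch phase.** The Missing data section for the smartphone test lets a missing value change phase only if it lies in the baseline or early in the intervention. That agrees with a re-draw of the A-to-B change point alone.

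**The concern.** A randomisation test asks how the observed statistic ranks among the values it would have taken under the other assignments that could have been drawn. It can speak about a phase only if those assignments move observations into or out of that phase. Here the random draw decides where A ends and B begins. The nine recorded follow-up values stay in phase C whichever start is drawn.

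The Abstract includes the follow-up tests in the primary endpoint, and each participant supplies nine of them. A p-value labelled baseline versus follow-up may well be read as showing whether a benefit survives 12 weeks without stimulation. If the number reflects only baseline and early-intervention data, that reading could be wrong in both directions: a real late effect is missed, or a benefit that has gone is reported as retained.

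**Working it through.** **Number of admissible starts.** The Sample size section gives a lowest p of 0.05 from 20 permutations. That follows from counting 5 to 24: 24 − 5 + 1 = 20 and 1/20 = 0.05. The Study design window gives 24 − 9 + 1 = 16, and the trimmed baseline gives 20 − 5 + 1 = 16, so the lowest p is 1/16 = 0.0625. I use 16 below. This conflict is a separate matter, and the algebra holds for either count.

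**Algebra.** Let k = 9, …, 24 be the candidate baseline length, A_k the values 5 to k, and C the nine follow-up values. The A-versus-C analogue of the named statistic is d_k = mean(A_k) − mean(C). For the length actually drawn,

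d_k − d_obs = [mean(A_k) − mean(C)] − [mean(A_obs) − mean(C)] = mean(A_k) − mean(A_obs).

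mean(C) drops out of every comparison. The one-sided p-value in either direction is the rank of mean(A_obs) among the 16 candidate baseline means.

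**One series, many follow-ups.** A single simulated A/B series (k = 14; candidate baseline means from 0.173 to 0.629) was paired with follow-up means from about −1000 to +1000. The signed p-values stayed at 0.0625 and 1.0000 throughout. With |d_k| instead, p was 1.0 at a follow-up mean of −0.199, 0.875 at 0.234, 0.1875 at 0.332 and 0.0625 at 0.666. Outside the range of baseline means it settles at one of the two one-sided values.

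**Many series.** Over 4,000 simulated series, replacing the follow-up data changed the signed p-value in 0 and the absolute-difference p-value in 2,424.

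**Rejection per participant, level 1/16 = 6.25%** (independent normal data, SD 1):

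- 3-SD effect in follow-up only: about 5% to 7% in separate runs, which is the null rate.
- +1 SD in phase B, absent or reversed at follow-up, signed statistic: about 19%.

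**Pooled over 15 participants** (sum of p-values at level 0.05, 1,500 runs; the pooling rule is my assumption, used only to show size; the signed test is one-sided towards higher values after baseline):

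| Effect in B (SD) | Effect in C (SD) | A vs C, signed | A vs C, absolute |
|---|---|---|---|
| 0 | 0 | 0.045 | 0.045 |
| 0 | +1 | 0.059 | 0.043 |
| 0 | +3 | 0.042 | 0.049 |
| 0 | −3 | 0.044 | 0.052 |
| +1 | 0 | 0.891 | 0.002 |
| +1 | +1 | 0.903 | 0.852 |
| +1 | −3 | 0.909 | 0.000 |

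The simulation error near 0.05 is √(0.05 × 0.95 / 1500) ≈ 0.006, so the first four rows do not differ from the nominal level. In the last three rows the signed test rejects at about 0.9 whatever happens at follow-up.

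**The case against.** **The statistic for A versus C is not spelled out.** This is the strongest objection, and part of it stands. The named statistic is for A versus B, and sidedness is open. A reader might infer that the p-value ignores the follow-up data under any statistic. The documents do not support that: with an absolute difference it can change with C, and the table shows it separating a lost effect (0.002) from a kept one (0.852) when phase B also moves. The false appearance of persistence is therefore specific to the signed form. Even so, the absolute form has no power when the effect lies only in follow-up, so it does not rescue the comparison.

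**The reference set for A versus C is not described.** That is true. Under another start, phase C would have fallen on other dates, but no data exist for those dates. Only the nine recorded values are available, and the draw does not reassign them. Joining A and C into one series and moving a cut through it would shift follow-up points, but through assignments the design could never have produced.

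**The test is valid for its stated null.** This stands. The null is that NMES has no effect on cognitive function, and under no effect at all the level is kept. The article does not say that this p-value will be used to claim persistence, so the misreading is a risk and not a stated intention.

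**A learning trend.** A reader might add that learning alone drives this p-value through baseline length. With a noiseless learning curve, p is 0.0625, 0.5 and 1.0 for baselines of 9, 16 and 24, but A versus B gives exactly the same values. That is no argument specific to follow-up, and I do not rely on it.

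**Conclusion.** The point holds in limited form. As written, with the signed mean difference and a randomised A-to-B change point, the baseline-versus-follow-up p-value carries no information on retention. That part is algebra and needs no distributional assumption. With an absolute difference the p-value can respond to follow-up, yet a follow-up-only effect is still rejected at about the null rate.

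The sizes (about 19% per participant and about 0.9 pooled for a 1-SD intervention-phase effect lost or reversed by follow-up) rest on independent normal data, 16 starts, the signed statistic and, for the pooled figure, a sum-of-p rule. Other effect sizes or serial correlation would change these figures but not the cancellation.

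A reader might infer that the false-positive rate is inflated or that the primary analysis fails. Neither follows from this point: the level is kept under the null of no effect at all, and the named A-minus-B statistic does not use phase C.

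**What to change.** In the Randomization test section, restrict the randomisation test to A versus B. Report A versus C descriptively for each participant, as a mean difference together with the nonoverlap measure (NAP) already planned between phases under Effect size measures. Add one sentence saying that persistence at follow-up is not tested by randomisation.

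The change is one of wording and needs no new data. One p-value per participant is dropped, and retention becomes a descriptive result.

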##### Visual analysis

First, measurement points will be plotted and visually inspected per participant. Six features will be visually examined according to the guidelines of Lane and Gast (2014): cognitive performance in the different phases, variability in cognitive performance both within and between phases, trends in the data, immediacy of effect, overlap of data points between phases, and consistency of data patterns across participants [57]. Instead of inspecting only immediate effects, also the existence of a potential delay of the effect and consistency of this delay between participants will be explored [58].

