### Sample size calculation

#### Single-case data

The sample size needed for the abovementioned statistical analyses is different for the SCED and single-armed prospective study design. For the SCED design, the minimum sample size is *n* = 1. Instead, the power of the analysis depends on the number of observations [40, 41]. For randomization tests the lowest attainable *p*-value is calculated by dividing 1 by the number of possible permutations. In this study, the baseline phase, after removing the first four values because of a learning effect, can contain 5 to 24 measurement points, allowing 20 possible permutations. This corresponds with a lowest attainable *p*-value of 0.05 [56]. Of note, successful replication of the single-case experiment in additional participants with similar symptoms will improve the generalizability of the results [40, 41].

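### The primary randomisation test may be repeated over lags until p is lowest, with no lag limit or adjustment, so the resulting p-value does not hold its error rate

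*Protocol article*

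**What the plan says.** Under Statistical analysis, the section Randomization test sets up a comparison of the baseline phase with the intervention and follow-up phases. Its statistic, the mean of phase A minus the mean of phase B, "will be chosen as the primary outcome of this study". The section then adds a step with a condition attached, worded as "In case visual analysis suggests delayed effects". Once that condition is judged to be met, the instruction is that "the randomization test will be repeated with lagged data until the lowest p-value has been reached (one effect lag equals one day". The section Visual analysis prepares for this by saying that "also the existence of a potential delay of the effect and consistency of this delay between participants will be explored".

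The article does not say what makes a plot suggest a delay, what lagging does to the data, how far the lag may go, whether the search is adjusted for, or whether a lagged p-value replaces the unlagged one. Study design states that neither participants nor researchers are blinded to phase. The false discovery rate correction is described only under Secondary statistics. The Randomization test section closes by citing studies in which the Type I error of the randomisation test in this type of design was acceptable.

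The size of the reference set is given in three places:
- Study design: a "random number generator in Excel set to give a random number between 9 and 24".
- Randomization test, after the first four measurements are removed: "leaving between 5 and 20 measurement points depending on the randomly decided length of the baseline period".
- Sample size calculation, Single-case data: the baseline "can contain 5 to 24 measurement points, allowing 20 possible permutations". The lowest p-value there "is calculated by dividing 1 by the number of possible permutations" and is stated as 0.05.

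**The concern.** A randomisation test is exact because the statistic is fixed before the data are seen and the observed start point is ranked among all start points that could have been drawn. The lag rule breaks this twice. An unblinded impression of the plots decides whether lags are tried at all, and the p-value itself then decides where the search stops. Reading that p-value against the ordinary reference set ignores both selections.

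The rule is attached to the test of the primary outcome. It is also tied to the aim in the Introduction of finding after how many weeks performance changes. When there is no effect, or only a weak one, the lag with the lowest p can reflect chance, and so can an onset time read from it. The cited assurance on Type I error refers to the randomisation test of this design; nothing in the article extends it to a lag chosen from the data.

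**Working it through.** **Step 1: the plan's own figure.** Lowest p = 1/K, where K is the number of possible start points. The sample size section uses 5 to 24 points: K = 24 − 5 + 1 = 20 and 1/20 = 0.05. The randomisation window gives K = 24 − 9 + 1 = 16. Removing four measurements leaves 5 to 20, so again K = 20 − 5 + 1 = 16 and 1/16 = 0.0625. The stated 0.05 is therefore not reproduced from the stated window; four was subtracted from the lower end only. K = 16 is used below, with K = 20 as a check.

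**Step 2: direction.** For any threshold a, P(min over lags of p ≤ a) ≥ P(p at lag 0 ≤ a), so a search can only raise the false-positive rate. For orientation, m independent tests at 1/16 give 1 − (15/16)^m: 22.8% for m = 4 (lags 0 to 3) and 56.8% for m = 13 (lags 0 to 12). Lags of one series are not independent, so the size needs simulation.

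**Step 3: size if the search is always run.** Inputs from the article: 16 start points, first four sessions removed, 36 intervention sessions, three sessions a week. Assumptions: no effect; AR(1) errors with correlation 0, 0.3 or 0.6; one- and two-sided tests; lag steps of one session; 20,000 series per setting. The article does not define lagged data, so two readings were run: the first intervention sessions are dropped, or the phase boundary is moved later. Entries are P(minimum p ≤ 1/16).

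| Lags searched | Early sessions dropped | Boundary shifted |
|---|---|---|
| 0 only | about 6% | about 6% |
| up to 3 sessions (1 week) | 8.5–9.6% | 18–22% |
| up to 12 sessions (4 weeks) | 13–16% | 50–58% |
| up to 24 sessions (8 weeks) | 20–21% | 78–86% |

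Typical values for 3, 6 and 12 sessions are about 9%, 12% and 15–16% (dropped) and 20–21%, 33–34% and 54–56% (shifted). Relative to 6.25%, 9% to 16% is a ratio of 1.4 to 2.6, and 20% to 56% a ratio of 3.2 to 9.0. If the search stops as soon as p first rises, the ratio is about 1.5–1.8 (dropped) or 3.0–4.8 (shifted).

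With K = 20 and threshold 0.05, the rate is 7–8% or 15–18% for one week of lags, and 11–14% or 42–48% for four weeks. The pattern does not depend on which K is right.

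**Step 4: the visual trigger.** If the trigger fires in a fraction g of participants without an effect, independently of the result (an assumption), the rate is 0.0625 + g(x − 0.0625), with x the always-run rate. For four weeks:
- Dropped, x = 0.137: g = 0.25 gives 0.081 (ratio 1.3); g = 0.5 gives 0.100 (1.6).
- Shifted, x = 0.54: g = 0.25 gives 0.182 (2.9); g = 0.5 gives 0.301 (4.8).

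**Step 5: the 0.05 level.** With 16 start points the smallest p is 0.0625 at every lag, so no single participant can reach 0.05 with or without the search. The harm appears at 1/16 or when participants are pooled. The article gives no pooling rule. If the 15 p-values were combined by Fisher's method (an assumption), the false-positive rate at 0.05 would rise from at most 0.005 at lag 0 to 0.09–0.22 (dropped) or 0.99–1.00 (shifted) for four-week searches.

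**Step 6: the lag unit.** With three tests a week, at most three of seven one-day steps can move a test across the boundary; the other four repeat the same split. This adds no inflation, but the unit is finer than the data.

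**The case against.** The fairest defence is that the study calls itself explorative, that a delayed effect is plausible, and that looking for a delay and its consistency across participants is sensible. That stands for the exploration. It does not cover a test of a null hypothesis on a named primary outcome, supported by a statement on Type I error, whose repetition stops at the lowest p.

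Three stronger readings are tempting, and the article does not support them.
- **A several-fold rise in false positives as a fixed result.** If early sessions are dropped and the search covers one week, the ratio is only about 1.4, and about 1.1 if the trigger fires in a quarter of participants. Ratios of 3 or more for searches up to 12 sessions come only from shifting the boundary, which the article never states.
- **The lowest lagged p-value as the reported primary result.** The article says the test is repeated; it does not say that the lagged p replaces the unlagged one. It does not exclude this either, and that gap needs closing.
- **False significance at 0.05 in single participants.** Under the stated window this cannot occur (Step 5). The 1/16 threshold is used here because it is the smallest attainable p; the article does not set it as a significance level.

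The lag unit is a minor matter of wording.

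**Conclusion.** The point holds. The article prescribes selection on the p-value for its primary test, triggered by an unblinded visual judgement, without a lag limit or adjustment. A p-value obtained this way is not valid, and the cited Type I error evidence is not shown to apply to it.

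The size is conditional: from about 6% to about 9–16% or about 20–56% for searches of 3 to 12 sessions. This rests on no effect, 16 start points, a search that is always run, and one of two assumed meanings of lagged data. The rise is smaller if the trigger seldom fires and larger if the search runs beyond four weeks. That the size cannot be stated more closely is itself a result of what the rule leaves open. A separate contradiction, 20 permutations against 16 start points, must be reconciled because it sets the smallest p that any version of the test can give.

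**What to change.** 1. In Randomization test, make the lag-0 comparison, or one single lag fixed before any data are seen, the only confirmatory analysis. With one fixed lag the simulated rate stays at its nominal value (0.058–0.065 against 0.0625).
2. Delete the clause that continues the search to the lowest p-value.
3. Report other lags and the onset time as exploratory and descriptive, without a claim of Type I control. Define what lagging does to the data and count lags in test sessions.
4. Reconcile the 20 permutations and minimum p of 0.05 in the sample size section with the 9-to-24 window.

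The change is one of wording. Its price is lower power at lag 0 for an effect that is truly delayed; that loss is not quantified here.

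A statistic maximised over a pre-specified list of lags and ranked over the possible start points would also be valid, but should be optional only, because it can be markedly conservative. In a small simulation with 16 starts and an immediate 1-SD effect, under the shifted reading, the chance of reaching 1/16 fell from about 27% at lag 0 to 4%, 3% and 2% for 3, 6 and 12 lags. Referring the minimum p to its own randomisation distribution gave null rates of 1.5–4.0% (dropped) and 0.0–0.4% (shifted) against 6.25%.

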##### Missing data

Missing values from the repeated smartphone-based cognitive test will be treated with the randomized marker method [62]. In this method, the missing value is removed from calculation of the mean in the randomization test. In addition, the position of the missing value will be randomly reshuffled within possible randomization schemes of the study protocol. In this study, this means that a missing value in the baseline or beginning of the intervention phase may be reshuffled to be part of the other phase if this falls within the possibilities (i.e. if it falls within the first 4 to 8 weeks of the study). This method was found to be more effective at controlling type I error and resulted in higher power than multiple imputation and single imputation using a time series model in a SCED simulation study [63].

#### Secondary data

For the secondary study parameters (i.e. BDNF levels and results of the oral cognitive test battery) which are measured within a single-armed prospective design, statistical analysis will be done using IBM SPSS Statistics 27.

##### Secondary statistics

Before analysis, the data will be checked for outliers, defined as values lying further than three times the interquartile range away from the median value. The normality assumption will be checked based on visual representations of the data using histograms and measurements of skewness and kurtosis (normality assumed if the data values lie between -2 and + 2) [64]. Homoskedasticity will be tested using the Levene’s test. Descriptive statistics will be used. Furthermore, the Friedman test will be used for analysis of repeated measurements. The False Discovery Rate (FDR) method will be applied to correct for the multiple testing problem. In the FDR method, every *p*-value is compared against a sequentially weighted threshold on all *p*-values [65].

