#### Study procedures

The experimental design is illustrated in Fig. 1. Upon the first appointment (T1), participants will sign an informed consent and undergo baseline examinations consisting of questionnaires and clinical tests. A smartphone application for repeated monitoring of cognitive function will be installed on their smartphones and they will be familiarized with the cognitive tests and neuromuscular electrical stimulation intervention. On a separate day (T2), within seven days from the first appointment, they will undergo a series of cognitive tests and venous blood samples will be collected. Furthermore, they will fill in a second list of questionnaires and undergo a clinical evaluation of strength and spasticity. This will be followed by a no-treatment baseline period with a random length of 3–8 weeks. Upon the third (T3), fourth (T4) and fifth (T5) visit, the oral cognitive tests, venous blood sample collection and questionnaires from T2 will be repeated. During the third visit (T3) the participants will receive their own NMES device for home-based training and they will be asked to return it 12 weeks later on the fourth visit (T4). All participants will undergo the same intervention. During the fourth visit (T4) the clinical evaluation of strength and spasticity that was done at T2 will be repeated. Between T2 and T4 and between T5 and T6 participants will undergo smartphone cognitive tests 3 times per week. At the end of the study, no additional tests will be done. Participants will be requested to write in a diary the specifications of the NMES session (duration, intensity) after each session and indicate when they performed a cognitive test. They can also write down any problems they encountered using the NMES device or smartphone application. Participants receive a telephone call once a week by one of the researchers to assess how they feel, be reminded of the diary and to assure there are no technical issues with the NMES device or smartphone application. Participants are allowed to withdraw from the study at any time. Available data from these participants will be included in the data analyses whenever possible.

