#### Oral cognitive test battery

At four time points, participants will undergo an oral cognitive test battery consisting of seven tests that were validated for repeated use in people with SCI, even with impaired hand function [43]. The Dutch version of these tests will be used, whenever the test depends on language. The tests have a good-to-excellent test–retest reliability, except the RAVTL recognition score which has been shown to have a poor test–retest reliability [43]. This test was still used as the interference recall and delayed recall scores of this test have a good test–retest reliability in people with SCI [43]. To further decrease learning effects of repeated administration of the cognitive tests, different versions will be used on different visits if available. The test versions will be numbered and on their first visit participants will be asked to draw a random number from an envelope including a number for every existing version of the cognitive test, until the envelope is empty. This is repeated for every cognitive test. The sequence will be reported for the next visits. The cognitive tests are presented in Table 1.

**Table 1 Tab1:** Oral cognitive assesments

Cognitive test	Description

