The baseline measurements of potential moderators of the effect of our intervention on cognitive and blood outcomes and risk factors for cognitive impairments according to a previous review paper will be entered in the statistical analysis [4]. The risk factors for cognitive impairments will be entered as a combined risk score with a maximum score of 10, indicating the highest risk. Participants receive a score between zero and one for each of the following: 1 point if self-reported history of TBI or mild to severe concomitant TBI according to TBI4 questionnaire [48], 0.5 points for a score of > 8/21 for anxiety and 0.5 points for a score of > 8/21 for depression on the HADS scale [51], 1 point for chronic pain indicated on the McGill pain questionnaire to exist longer than 3 months and is scored at its minimum a VAS score of 3 [50], 0.5 points for a history of autonomic dysreflexia and 0.5 points for a blood pressure below 90/60 upon measurement, 1 point for tetraplegic participants compared to 0 points for paraplegic participants, 0.33 points for self-reported sleep apnea, 0.33 points for a FVC value below 0.85% of the predicted value, and 0.33 points for a PCF below 4.5L/s, 0.25 points for regular alcohol use (more than once per week), 0.25 points for drug abuse, 0.25 points for polypharmacy (more than 7 prescribed drugs), 0.25 points for any medication acting on the central nervous system, 1 point for participants who finished only basic education, 0.5 points for participants who finished only secondary education, 0.5 points for diabetes mellitus, 0.5 points for a BMI equal to or above 25 kg/m^2^ [55], 1 point for previous intensive care admission.

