##### Missing data

Missing pre-post values will not be replaced by specific values, but be excluded from statistical analysis.

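### The only test named for the secondary outcomes, a Friedman test over T2 to T5, does not answer the before-versus-after-NMES question; for the oral cognitive tests, practice before treatment can make it significant

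*Protocol article*

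**What the plan says.** The Secondary data section covers "BDNF levels and results of the oral cognitive test battery) which are measured within a single-armed prospective design". Under Study design, the measurements are taken before the baseline phase (T2), then "at the end of the baseline phase, at the end of the intervention phase and at the start of the follow-up phase" (T3, T4 and T5). Under Study procedures, T2 is followed by an untreated interval: "This will be followed by a no-treatment baseline period with a random length of 3–8 weeks". The NMES interval is therefore T3 to T4, and T4 to T5 is the rest period.

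The Introduction states the secondary aim as change in BDNF before and after the intervention and after follow-up, and hypothesises a rise.

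Secondary statistics names one inferential test: "the Friedman test will be used for analysis of repeated measurements". A False Discovery Rate correction is added. Missing data (secondary) says: "Missing pre-post values will not be replaced by specific values, but be excluded from statistical analysis".

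On practice, the Oral cognitive test battery section says: "To further decrease learning effects of repeated administration of the cognitive tests, different versions will be used on different visits if available".

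**The concern.** The design has two visits before treatment, and with no control group the T2 to T3 change is the only untreated comparison before NMES starts. The Friedman statistic does not use it. All four visits are treated as exchangeable labels, so a gain that occurs entirely before NMES counts as much as a gain under NMES, and a fall counts as much as a rise. FDR does not help, because it corrects for how many tests are done and not for what each one measures.

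At stake is the reading of the secondary results. A significant Friedman result on a cognitive test could reflect familiarity with that test. A significant result for BDNF would not show when the level changed or whether it rose.

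Friedman also needs all four values from each participant. Someone who misses only T5 contributes nothing to the test, although the T3 to T4 change was observed.

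**Working it through.** **Inputs from the protocol article.** Planned N = 15; four time points; correlation among repeated measures at least 0.77 (0.77 used); effect size d = 0.71; power 0.80 (all under Sample size calculation and Study design). Versions available for four visits (Table 1): Stroop one, Digit Span and RAVLT two, SDMT and COWAT three. Each of these tests must therefore repeat at least one version.

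**Assumptions.** Two-sided alpha 0.05, the size of the practice gain and the rate of missed visits are not given for this analysis. The last two are shown as ranges.

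**The plan's own figure.** Repeated measures ANOVA, one group, f = d/2 = 0.355, m = 4, sphericity: λ = f²·N·m/(1 − ρ) = 0.1260 × 7 × 4 / 0.23 = 15.34, with 3 and 18 degrees of freedom. Power is 0.85 at N = 7 and 0.77 at N = 6, so the stated minimum of 7 reproduces. That calculation is also for an omnibus Time effect.

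**Invariance.** In simulated data, permuting the four visit columns left the Friedman rejection rate unchanged (0.667 before and after). The statistic carries no information on which interval moved.

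**Practice only, no NMES effect.** Normal data with equal correlations of 0.77, N = 15, 20,000 replicates. Means are (0, g, g, g) at T2 to T5, in SD units.

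| Step g at T3 | Friedman rejects | T4 − T3 rejects |
|---|---|---|
| 0 | 4.5% | about 5% |
| 0.2 | 13% | about 5% |
| 0.3 | 27% | about 5% |
| 0.4 | 46% | about 5% |
| 0.5 | 67% | about 5% |

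At g = 0.5, Friedman rejects 34% of the time if the correlation is 0.5 and 97% if it is 0.9.

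**Power if the effect is real.** For a true T3 to T4 change of 0.71 SD, the T4 − T3 test has 95% power (signed-rank) to 97% (paired t). Friedman has 99% if the gain persists to T5 and 94% if it is lost by T5. The targeted contrast therefore costs little power.

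**Practice that continues after T3.** If practice adds a further 0.2 or 0.3 SD between T3 and T4 with no NMES effect, the T4 − T3 test rejects about 18% or 35% of the time.

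**Difference of changes, (T4 − T3) − (T3 − T2).** Its power is about 58% at 0.71 SD with no practice. With a 0.3 or 0.5 SD practice step at T3 that then stops, plus a true 0.71 SD effect, power falls to about 25% or 9%. With that practice step and no NMES effect, it rejects in the unfavourable direction about 15% or 33% of the time.

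**Missed visits** (assumed independent, same rate at each visit). Expected complete sets of four are 15 × (1 − p)⁴; expected T3–T4 pairs are 15 × (1 − p)².

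- p = 5%: 15 × 0.8145 = 12.2 against 15 × 0.9025 = 13.5
- p = 10%: 15 × 0.6561 = 9.8 against 15 × 0.81 = 12.2
- p = 20%: 15 × 0.4096 = 6.1 against 15 × 0.64 = 9.6

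**The case against.** The strongest reply is that this is a short summary in a journal article, that pairwise follow-up tests are commonly left to an analysis plan, and that nothing says a significant omnibus result will be read as an NMES effect. The outcomes are secondary in a study that calls itself explorative. This stands to the extent that missing post hoc tests are not a fault here. The point concerns the test that is named: carried out as written, it cannot attribute a change to an interval or give it a sign.

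The second reply is that T4 minus T3 is no cure, because practice may continue after T3. That also stands, and the 18% to 35% above measures it. The contrast removes practice gained before T3, not all practice.

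Some stronger readings are tempting but not supported:

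- A reader might infer that complete-case exclusion contradicts Study procedures. That section says "Available data from these participants will be included in the data analyses whenever possible", and the qualifier allows exclusion where a test needs complete data.
- A reader might infer that the plan fails because Friedman takes no covariates while the moderators and risk score "will be entered in the statistical analysis". That sentence does not tie them to Friedman, and Study design links moderators to the individual single-case courses. Adding the score as a plain covariate would not test moderation either.
- A reader might want SDMT set aside because it resembles the smartphone task. The smartphone task is also practised 9 to 24 times before T3, the Fig. 1 legend expects the fast gain in roughly the first three sessions, and SDMT is verbal. Removing it is a preference, not a correction.

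**Conclusion.** The point holds in a limited form. The named test does not answer the before-versus-after question for any secondary outcome. For the oral cognitive tests, a retained practice gain of 0.3 to 0.5 SD before treatment would by itself make the test significant about 27% to 67% of the time. These sizes rest on the assumed practice step, alpha 0.05, normal data and the stated lower bound of 0.77 for the correlation. The direction of the finding does not depend on them.

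A reader might extend the practice argument to BDNF. A serum assay has no practice effect, so for BDNF only the missing interval and direction remain. A reader might also take it that a missed visit removes the participant from the trial's analysis. It removes them only from the affected Friedman tests; the smartphone single-case analysis is untouched.

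The change should be made, but it concerns secondary outcomes and does not affect the primary analysis.

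**What to change.** Pre-specify T4 minus T3 as the key contrast for each secondary outcome. Estimate it from a mixed model with visit as a categorical factor, participant as a random effect and all available visits, or use a paired signed-rank test if the planned normality check fails. Report the T2 to T3 change beside it as the untreated reference, and T5 minus T3 for persistence. Apply FDR to the key contrasts and keep Friedman as a sensitivity analysis.

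Show (T4 − T3) − (T3 − T2) descriptively only: its power is low, and it is biased against NMES if practice stops after T3.

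The cost is analysis wording; the visits are already scheduled. There are two downsides to state in the plan: the model brings a distributional assumption, and in a single arm T4 minus T3 still includes any practice after T3. A cognitive gain should therefore not be presented on its own as proof of an NMES effect.
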